### Study design

Infants meeting inclusion criteria are identified and their parents approached for consent. After informed written parental consent is obtained, infants are randomized 1:1 by a software-generated list in one of the following groups:Control group: Adjustable Fortification with commercial multi-component fortifier (FM85 Nestlè) and protein concentrate (Protifar Nutricia), named BMC and BPC respectively, derived from bovine milk, for a minimum of 21 days (if necessary, fortification is continued after this period using the same type of product)Fortilat group: Adjustable Fortification with multi-component fortifier and protein concentrate derived from donkey milk, named DMC and DPC respectively, not commercially available, and prepared according to current EU legislation on Foods for special medical purposes, for a minimum of 21 days (if necessary, fortification is continued after this period using the same type of product).

The composition of BMC and DMC are provided in Table 1. Table 2 presents the composition of BPC and DPC. The experimental products were produced by ultrafiltration of pasteurized donkey milk in a pilot stainless steel plant. Retentates from the ultrafiltration processes were then pasteurized and aseptically lyophilized and packed. All the batches used for the trial were analyzed for the microbiological and chemical profile and complied with the safety criteria required by Italian legislation. The products are stored at −80 °C until used.

**Table 1 Tab1:** Macro-composition of the multi-component fortifiers derived from bovine milk (BMC) and from donkey milk (DMC). Values per 100 g of product

	BMC	DMC
Protein g (Nx6.25)	20.0	22.5
Carbohydrate g	66.0	59.0
of which:		
Lactose g	6.0	59.0
Maltodextrine g	60.0	0.0
Fat g	0.4	3.6
Energy:		
Kcal	385	390
kcal/g protein	18.8	15.6
Calcium mg	1500	938
Phosphate mg	900	734
Osmolality mOsm/Kg	453	441

**Table 2 Tab2:** Composition of the protein concentrates derived from bovine milk (BPC) and from donkey milk (DPC). Values per 100 g of product

	BPC	DPC
Protein g (Nx6.25)	88.5	43
Carbohydrate g	<1.5	33.5
Fat g	≤2.0	6.1
Energy Kcal	370	418
Calcium mg	1350	1650
Phosphate mg	700	1150

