### Outcome measures

Primary Endpoint.Occurrence of at least one episode of feeding intolerance, defined as interruption of enteral feeding for at least eight consecutive hours during the observation period.Secondary Endpoints.2.1 Gastrointestinal outcomes: Number of feeding intolerance episodes, number of feeding interruption episodes (of any duration), total hours of enteral feeding interruption, time required to reach full enteral feeding (150 ml/kg/day).2.2 Gastric Emptying time (ultrasonic measurements of the antral cross sectional area) [25, 26]: half-time of gastric emptying (minutes) and time of gastric emptying (minutes).2.3 Esophageal impedance and pH monitoring (MII/pH) [27, 28]: GER frequency (reflux events/h), bolus reflux extent (number of channels), Bolus clearance time (seconds), bolus exposure index and reflux index (percentage).2.4 Clinical outcomes: necrotizing enterocolitis, suspected or confirmed sepsis, mortality, hospital stay duration, intraventricular hemorrhage, retinopathy of prematurity (defined according to the Vermont Oxford Network) [29].2.5 Metabolic and auxological outcomes (as shown in the synoptic table) (Table 5).

**Table 5 Tab5:** Synoptic table. T0: before starting the fortification; T1: day 7 after beginning the fortification (if level 3 of ADJ fortification) or as soon as level 3 is reached; T2: day 14 since beginning of fortification; T3: day 21 since beginning of fortification

	STUDY PERIOD						
	Enrolment	Allocation	Post-allocation				Close-out
Timepoint			T0	T1	T2	T3	
Enrolment:							
Eligibility screen	X						
Informed consent	X						
Full patient history collection	X						
Allocation		X					
Intervention:							
BUN			X	X	X	X	
Albumin			X	X	X	X	
Creatinine			X	X	X	X	
Calcium			X	X	X	X	
Phosphate			X	X	X	X	
Alkaline Phosphatase			X	X	X	X	
Weight			X	X	X	X	
Lenght			X	X	X	X	
Head circumference			X	X	X	X	
Plasma Aminoacids			X			X	
Urine Aminoacids			X			X	
Urinary Metabolomic Profile			X			X	
Calprotectin			X			X	
pH			X	X	X	X	
BE			X	X	X	X	
HCO_3_^−^			X	X	X	X	
MII/pH						X	
Gastric emptying time						X	
Assesments							
List other data variables							X
List other data variables							X

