### Statistical analysis

The statistical analysis will be performed by the Medical Statistics and Biometry Unit of the Clinical and Community Sciences of the University of Milan.

At the end of the recruitment, the occurrence of the primary endpoint will be evaluated on the intention-to-treat population (all randomized infants). The comparison between the two study groups will be performed with the exact Fisher test. All secondary endpoints will be modelled in the framework of generalised linear model [30] allowing, when appropriate, for relevant covariates. The number of episodes of feeding intolerance (0, 1 … k) will be modelled as a Poisson variable. Total hours of enteral feeding interruption, time required to reach full enteral feeding, hospital stay duration, gastric emptying time and MII/pH parameters will be modelled (after proper scale transformation, if required) as normal variables. The occurrence of clinical outcomes, assesed as dychotomous variable (yes/no) will be modelled as binomial variables. Metabolic and auxological outcomes, which are repeatedly during study period, will be modelled (after proper scale transformation, if required) as normal variables, with a model allowing for repeated measures. All statistical models are fit with SAS software [31].

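### The count of feeding intolerance episodes is fixed as Poisson with no allowance for dispersion, so the test's true error rate depends on an unchecked variance assumption

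*Protocol article*

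**What the plan says.** Outcome measures, item 2.1, opens the list of secondary gastrointestinal outcomes with "Number of feeding intolerance episodes, number of feeding interruption episodes (of any duration), total hours of enteral feeding interruption". An intolerance episode takes its meaning from the primary endpoint, where it is "defined as interruption of enteral feeding for at least eight consecutive hours during the observation period".

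The Statistical analysis section sets the general frame: "All secondary endpoints will be modelled in the framework of generalised linear model [30] allowing, when appropriate, for relevant covariates". For the count it then fixes the distribution: the number of intolerance episodes "will be modelled as a Poisson variable". It names no scale parameter, robust variance or alternative count model. For the outcomes treated as normal, the same section does provide for a change of scale where needed, and for outcomes measured repeatedly it provides a repeated-measures model. The count has no comparable safeguard.

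The primary endpoint is the yes/no occurrence of an episode, and for it "The comparison between the two study groups will be performed with the exact Fisher test".

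**The concern.** Under a Poisson model the standard error of the log rate ratio follows from the total counts alone. It does not respond to how the episodes are spread over infants. If a minority of infants have several episodes each, the real sampling variance exceeds what the model reports, confidence intervals are too short and p-values too small. If second episodes are rare, the error runs the other way and the test loses power.

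The eligibility criteria admit infants under 32 weeks or under 1500 g with no lower limit, so infants of quite different maturity share one rate per arm unless a covariate separates them. That makes excess variation plausible. At stake is the credibility of any claim, in either direction, about the number of intolerance episodes. This matters because the Discussion would treat improved feeding tolerance as a major advance.

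**Working it through.** **The plan's own figure.** The protocol gives no figure for the count endpoint. Its only calculated figure is 62 per group for the binary primary endpoint. With 45% against 20% (the 25% reduction read as percentage points), two-sided 5% and 80% power:

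- mean proportion 0.325; n = [1.96 × √(2 × 0.325 × 0.675) + 0.8416 × √(0.45 × 0.55 + 0.20 × 0.80)]² / 0.25² = (1.298 + 0.537)² / 0.0625 = 53.9
- with continuity correction: (53.9/4) × [1 + √(1 + 4/(53.9 × 0.25))]² = 61.6, that is 62.

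So 62 per arm is used below.

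**Inputs from the protocol.** About 45% of infants with at least one episode, so P(0) = 0.55; 62 per arm; 1:1 allocation; 5% type I error (taken as two-sided).

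**Input not in the protocol.** The variance/mean ratio φ of the count is an assumption, so a range is shown.

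**Formula.** With the same φ in both arms and no treatment effect, the true standard error is √φ times the Poisson one. The real size of the nominal 5% test is then about 2 × [1 − Φ(1.96/√φ)].

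**Over-dispersed side.** Take negative binomial counts with dispersion k, holding P(0) at 0.55. Then the mean is μ = (0.55^(−k) − 1)/k and φ = 1 + kμ = 0.55^(−k). The last column comes from 40,000 simulated trials per row, without covariates.

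| k | μ | φ | √φ | size, formula | size, simulated |
|---|---|---|---|---|---|
| 0 (Poisson) | 0.598 | 1.00 | 1.00 | 5.0% | 4.8% |
| 0.25 | 0.645 | 1.16 | 1.08 | 6.9% | 6.7% |
| 0.5 | 0.697 | 1.35 | 1.16 | 9.1% | 8.9% |
| 1 | 0.818 | 1.82 | 1.35 | 14.6% | 14.1% |
| 2 | 1.153 | 3.31 | 1.82 | 28.1% | 27.4% |

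The last row implies 1.153/0.45 = 2.6 episodes per affected infant. It is an extreme case.

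**How little heterogeneity is needed.** Suppose half the infants have a 30% chance of at least one episode and half have 60%, averaging 45%, with Poisson counts within each half. The rates are −ln 0.70 = 0.357 and −ln 0.40 = 0.916, with mean 0.637 and between-half variance (0.560/2)² = 0.078. So φ = 1 + 0.078/0.637 = 1.12 and the size is about 6.4%. With 20% and 70%, φ is 1.34 and the size about 9%. These splits are also assumed.

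**Under-dispersed side, equally compatible with 45%.**

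- No infant has a second episode: mean 0.45, variance 0.45 × 0.55 = 0.2475, φ = 0.55, size 0.8%.
- 35% have one episode and 10% have two: mean 0.55, variance 0.75 − 0.55² = 0.4475, φ = 0.81, size 3.0%.

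**After the change.** In simulation at 62 per arm, a Pearson-scaled standard error kept the size at about 4% to 5% across both sides of this range. A robust standard error gave about 4% to 6%, rising to 6.7% at still stronger over-dispersion (k = 3, φ = 6.0).

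**The case against.** The strongest objection is that this is detail for a statistical analysis plan that is not shown. A scale parameter, a robust variance and covariates all fit within the stated generalised linear model, and naming Poisson for a count in a condensed article is not an error in itself. That is largely fair, and it keeps the point modest. It does not remove it: the article commits to a distribution and gives other outcome types a safeguard that it does not give this one.

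Several stronger readings are tempting, and the document does not support them:

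- *The counts are over-dispersed, so the p-values will be too small.* The 45% figure fits over-, equal and under-dispersion alike. That one episode predicts another is nowhere stated.
- *The stated model ignores maturity.* Covariates are already permitted. Gestational age could absorb part of the heterogeneity, and the unadjusted simulations above treat all of it as unexplained.
- *Unequal exposure makes it worse.* Products are given "for a minimum of 21 days (if necessary, fortification is continued after this period using the same type of product", which might suggest varying time at risk. But that describes how long the product is given. Scheduled measurements in Table 5 end at day 21, the Abstract speaks of 21 days, and the loss-to-follow-up section expects little loss and very rare early transfer. This is weak evidence for a missing exposure term.
- *Both counts in item 2.1 are affected.* The Poisson sentence covers intolerance episodes only. It assigns no model to interruptions of any duration.
- *This is the key supporting endpoint.* The protocol lists it among several secondary outcomes and does not rank it.

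**Conclusion.** The point holds in conditional form. The protocol ties inference on the intolerance-episode count to variance equal to the mean, without a check. If that fails, the stated 5% is wrong: about 7% to 14% for variance/mean ratios of 1.16 to 1.82, about 27% at 3.3, and about 1% to 3% for ratios of 0.55 to 0.81. These figures rest on an assumed dispersion, 45% affected in both arms, 62 infants per arm and no covariate adjustment. Over-dispersion is the more plausible direction given the mixed population, but the document cannot settle it. The consequence is confined to one secondary endpoint.

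**What to change.** Keep the log-linear model for the number of feeding intolerance episodes and prespecify a Pearson-scaled (quasi-Poisson) standard error, or a robust one. Pearson scaling is the better first choice, since it stayed closest to 5% and corrects in both directions. Negative binomial regression can be named as an alternative if the counts turn out over-dispersed; it cannot represent under-dispersion. Name gestational age as a covariate, which the section already allows.

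The cost is one sentence and a model option. Intervals on the log scale change by √φ: practically unchanged if the Poisson assumption holds, 8% wider at a ratio of 1.16, 35% wider at 1.82, and narrower if repeat episodes are rare. No additional infants or data are needed.

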## Discussion

We present the protocol of a study aimed to assess the effects of a new human milk fortifier derived from donkey milk on VLBWI feeding tolerance and growth. To the best of our knowledge, this trial is unique, being the first study that investigates the use of a human milk fortifier derived from donkey milk for the nutrition of preterm and VLBWI.

In our trial all the infants received exclusively human milk (Fresh own mother’s milk or Pasteurized donor milk) without any preterm formula supplementation. The trial of Sullivan, comparing a human milk based fortifier with a bovine milk based fortifier, included in the group supplemented with the bovine fortifier also subjects fed with preterm formula [32]. This represents a confounding variable masking the effects of the two different fortifiers as a sole supplement of human milk.

If the donkey milk derived fortifier will be proved to improve the feeding tolerance or some of the other outcomes (clinical, metabolic, neurological or auxological) of very preterm and VLBWI, it would be an absolute innovation in the field of feeding practices for preterm infants.

A possible limitation of our study is that it has been designed as a single-blind randomized controlled trial, being the caregivers aware of infants’ allocation in the study. To try to eliminate any possible bias, a protocol about the evaluation of the signs of feeding intolerance has been introduced in our unit before the beginning of the study. A strict adhesion to the protocol was recommended to all the nursing staff.

## Abbreviations

ADJ: Adjustable Fortification
BMC: Multi-component fortifiers derived from bovine milk
BPC: Protein concentrates derived from bovine milk
BUN: Blood urea nitrogen
DMC: Multi-component fortifiers derived from donkey milk
DPC: Protein concentrates derived from donkey milk
GER: Gastroesophageal Reflux
MII/pH: Multichannel Intraluminal Impedance and pH monitoring
NICU: Neonatal Intensive Care Unit
SDS: Standard deviation score
VLBWI: Very Low Birthweight Infants
